### Randomization

The 21 participating clinics will first be divided into two groups based on the poverty level of the catchment area and expected enrollment of individuals with FEP for each clinic. The largest site will be matched with two clinics of a similar poverty level and clinic size as well, as noted above. The matching will be done based on a visual inspection of a scatter plot of expected enrollment by the income of each site. Then, blocks of size 2, and one block of size 3, will be randomly generated. Randomization will be performed using a randomization scheme generated by SAS 9.4. This procedure will entail (1) generating a random number 0 or 1 ten times, and (2) assigning 0 to the Usual FEP care clinic and 1 to the OTCH clinic in each matched pair. For the block of size 3, two sites will be assigned to either OTCH or Usual FEP care, and the remaining site to either OTCH or Usual FEP care as well. The statistician will notify the contact-PI once the randomization is done, and he will then call the CMHC Director to inform him/her of the assigned treatment status, followed by a written note to the Director with the same information. The random allocation within blocks of two will enable us to bring into the study one OTCH and one Usual FEP Care CMHC per month. We note that the randomization (and notification) will be done at the start of the project, which will enable us to select equal numbers of OTCH and Usual FEP Care CMHCs for data collection (at organizational, provider, and participant level) during the preparatory phase.

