After a site enters the study, the participating clinic will be asked to refer all individuals with FEP to our study team. A health provider in each of the participating clinics will be designated to be the local point person for the coordination of recruitment and follow-up of study participants in his/her site; this role will be referred to as “Local Coordinator.” As noted previously, an FEP registry is in place in Chile to identify individuals with an FEP to ensure they receive timely and appropriate treatment. The Local Coordinators can use that database to identify potential participants at their clinics. Using this tool, the Local Coordinator will assign a numeric screening ID number to each potential participant and maintain a log with this information in a secure cabinet in each site. Each site will be assigned a numeric range (1000s, 2000s, 3000s, etc.). The Local Coordinator, who is not part of the OTCH research team, will contact the potential participants by phone, videoconference, or in-person when possible. If verbal consent is obtained, the Local Coordinator proceeds with a brief introduction to study. The Local Coordinator will briefly explain that he or she can participate in a research study and will describe the study’s purpose. If the client accepts to participate, the Local Coordinator will notify a member of the Research Team, known as the Registration Designee, who will oversee assessing the capacity of consent and administering the informed consent form. If someone serves as a Registration Designee for the participant, this person will not be allowed to serve as an interviewer for this participant in order to maintain the blind. This process will take place remotely unless the clinic is open for in-person appointments. Once consent is obtained, an interviewer will be notified so he/she can contact the potential participant and conduct the baseline assessment. Similar procedures will be followed for minors, and for providers, policy makers, health directors, and family members who participate in the study.

Following the recommendations by McRae et al. [17] and Giraudeau et al. [18] on administering consent forms in cluster RCTs, there will be two different consent forms: one for participants from intervention clinics and another one for participants from controls clinics. In addition, we will have other consent forms for policy makers, health directors, providers, and family members.

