Interviewers who conduct both the clinical assessments and qualitative interviews will be mental health professionals with prior research training and experience conducting clinical assessments. They will be trained on research and assessment procedures by the Research Team through 3 on-line, videoconferencing sessions. The first session will entail going over the research protocol and the interviewer’s manual. The second session will address the required procedures to enter data into RedCap and report adverse events. Finally, in the third session, a thorough review of the quantitative and qualitative measures will take place, with special emphasis in the administration of the clinical-based measures such as the PANSS.

The risks to participants are minimal, and the measures we will take, combined with rigorous team training, will reduce them even further. In case of emotional upset and/or suicide feelings, immediate action will be taken, such as a referral for mental health and suicide risk assessment and appropriate counseling at usual health services in Chile.

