#### For the qualitative assessments

We will use qualitative methods to identify and characterize potential barriers/facilitators and processes that may inform the implementation of OTCH and its continuous adaptation process. In particular, we will explore factors at multiple levels (system-, organizational-, provider- and client/family member-level) by conducting semi-structured, on-line qualitative interviews with policy makers, director/health managers, and providers and focus groups or qualitative interviews with users and family members.

Qualitative interviews and focus groups will be conducted when OTCH teams begin enrollment activities and at 6- and 18-month post-randomization at all OTCH sites and at five sites randomized to usual care. We will conduct these interviews and focus groups via telephone/teleconferences. All interviews and focus groups will be audio recorded with participant’s informed consent. We will employ a purposive sampling approach to identify and invite key informants representing each group of participants [16–18].

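### The blinding rule excludes the consenting staff member participant by participant, but allocation is by clinic, so PANSS raters can readily learn the arm

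*Protocol article*

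**What the plan says.** All references are to the protocol article.

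- **Allocation (Randomization).** Clinics are randomized in matched pairs plus one block of three, by "assigning 0 to the Usual FEP care clinic and 1 to the OTCH clinic in each matched pair".
- **Blinding rule (Recruitment).** The Registration Designee, a research team member, assesses capacity and administers consent. If someone has done this for a participant, "this person will not be allowed to serve as an interviewer for this participant in order to maintain the blind". The article states no other blinding rule for interviewers.
- **Consent forms (Recruitment).** There are two client forms: "one for participants from intervention clinics and another one for participants from controls clinics".
- **Interviewers (Recruitment).** The text describes a single group, "Interviewers who conduct both the clinical assessments and qualitative interviews", whose training puts "special emphasis in the administration of the clinical-based measures such as the PANSS".
- **Qualitative work (For the qualitative assessments).** Interviews and focus groups explore barriers, facilitators and processes bearing on OTCH implementation. They run when OTCH teams begin enrolling and at 6 and 18 months, "at all OTCH sites and at five sites randomized to usual care".
- **Ratings (Table 4).** The PANSS is scheduled at baseline, 12 and 24 months. The same table schedules ten questions on receipt of services central to OTCH at those time points.
- **Staffing (Study management).** One research team is responsible for all quantitative and qualitative data collection.

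**The concern.** The rule exists because handling consent discloses the arm. In an individually randomized trial, keeping that person away from that one participant would be enough. Here every participant at a clinic shares its arm, so the knowledge gained from one consent applies to the whole clinic while the exclusion covers one person. Someone can follow the rule exactly and still rate other participants of that clinic knowing their arm.

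The qualitative work is a second route to the same knowledge. It is about OTCH, it precedes the follow-up ratings, and the interviewers who do it come from the pool that administers the PANSS.

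At stake is the Aim 2a comparison of psychotic symptoms and, because it uses the 24-month clinical outcomes, the Aim 2b mediation analysis. The PANSS is a severity rating that depends on the judgement of the person administering it. A rater who knows the arm may, without intending to, score in favour of the new programme.

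**Working it through.** No stated figure depends on the blinding rule, so there is nothing to reproduce. The check sets the provisions side by side.

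**1. What one consent discloses.** The client forms are arm-specific, so the designee learns that participant's arm. Allocation is by clinic, so this is the arm of all participants there. Average clinic size is 300/21 = 14.3, or about 14, so the rule covers one participant and leaves about 13 others uncovered.

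**2. How often that could matter (illustration on assumed staffing).** The article does not give the number of staff. Suppose R people share the designee and interviewer roles at random. The chance that a participant's interviewer was designee for at least one of the other 13 at that clinic is 1 − (1 − 1/R)^13:

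| R (assumed) | Probability |
|---|---|
| 5 | 0.945 |
| 10 | 0.746 |
| 20 | 0.487 |

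This counts all consents at the clinic, so it fits the 24-month rating best. Recruitment was planned from March 1, 2021 to December 1, 2022, which is 21 months, so even the first participant's 24-month rating falls after the last planned consent. At baseline and 12 months, fewer consents may have taken place. If the two roles are in fact held by separate people, the probability is zero by this route.

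**3. The qualitative route.** Start-up and month 6 precede the 12-month rating, and month 18 precedes the 24-month rating. With 21 clinics, nine pairs and one block of three give arms of 10 and 11. Qualitative work covers all 10 or 11 OTCH clinics but only five of the 11 or 10 usual-care clinics (5/11 = 45% or 5/10 = 50%). Exposure by this route is therefore uneven between arms.

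**4. Is there a provision that closes the gap?** The article does not separate raters by clinic, does not separate qualitative interviewers from PANSS raters, and does not provide for central masked rating.

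**The case against.** The strongest reply is that the article describes a pool of interviewers and their training, not who works where. It mentions an interviewer's manual that is not shown, and assignment to clinics may be settled there. The article nowhere says that one person does consent, qualitative interviews and PANSS ratings at the same clinic. This stands against any claim that assessors will know the arm, which a reader might infer but which the text does not establish. It does not rescue the rule. The article states both the rule and its purpose, and its wording allows what it is meant to prevent.

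Other stronger readings also fail:

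- **Site-coded IDs.** A reader might conclude that the clinic is visible on every record, since ID ranges are site-specific. The text describes a screening ID that the Local Coordinator, who is outside the research team, assigns and logs. It does not say that this ID appears on assessment records or that interviewers see it.
- **Functioning and the other scales.** The article does not say that the SRFP is interviewer-rated. Several other scales record users' own views, and fidelity rests on provider feedback, supervision calls and site visits. Rater bias is clearly supported for the PANSS only.
- **Qualitative interviews as proof of arm.** Five usual-care sites have them too, and some informants are policy makers, so doing such interviews does not by itself identify the arm. It is the OTCH-focused content that makes the arm easy to learn.
- **A size for the bias.** One could assume a rater shift of 0.1 to 0.2 SD and compare it with the planned d = 0.35 (0.1/0.35 = 29%; 0.2/0.35 = 57%). That only restates the assumption; nothing in the documents supports those shifts.

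**Conclusion.** The point holds in a limited form. The only stated safeguard works at participant level while allocation works at clinic level, so full compliance still lets a person who knows a clinic's arm rate its participants. Shared use of interviewers for OTCH-focused qualitative work adds a second opening. Interviewers can readily learn the arm; the documents do not show that they will.

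The consequence is possible rater bias in at least the PANSS. Clinical effectiveness is a secondary aim here, and the primary outcomes are implementation and service measures, which limits the weight of the point. The size of the bias is unknown. The probabilities above describe the chance of exposure under assumed random role-sharing, not the amount of bias. The conclusion itself rests on no assumed number, only on clinic allocation, arm-specific forms and the wording of the rule.

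**What to change.** Restate the exclusion by clinic. For all assessments still to be done, anyone who has administered consent or conducted qualitative interviews or focus groups at a clinic does not rate the PANSS for any participant of that clinic. Within the visit, give the PANSS before the questions on services received, so that the answers do not reveal the arm first. If the unpublished interviewer's manual already arranges this, the article's rule should be reworded to match.

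The cost is mainly reassigning existing interviewers across clinics. This is feasible because most contacts are remote, but it reduces scheduling flexibility. The number of interviewers is not given, so it cannot be confirmed from the article that reassignment alone will cover every clinic. Recruitment was already under way, so ratings already made cannot be changed. Where the clinic-level rule was not or cannot be met, report those PANSS ratings as not blinded.

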### Data collection

#### For the trial

Table 4 provides a description of all the measures that will be used in the trial. All instruments will be administered at baseline 12 and 24 months. Selection of measures was guided by the PhenX toolkit for clinical measures in early psychosis and key moderators that are known to influence the implementation of evidence-based practices [19]. All measures will be translated into Spanish if a Spanish language version is not available using the WHO guidelines for translating and adapting measures.

**Table 4 Tab4:** Study assessments

	Construct	Group	Measure description	When	Time
Implementation outcomes	Fidelity	Providers, families, and participants	Adapted version of the OTNY fidelity scale. The scale assesses the degree to which FEP services deliver evidence-based practices. Fidelity assessment will be based on providers’ feedback, supervision calls, and site visits. Site visits have been established as a best practice for fidelity assessment [20].	6, 12, 24 months	NA
	Acceptability	Providers	Providers’ attitudes to evidence-based practices will be measured by the *Evidence-Based Practice Attitude Scale* (EBPAS) [21]. The EBPAS consists of 15 items rated on a five-point scale from 0 (“Not at all”) to 4 (“Very great extent”). Range: 0–60 points.	Baseline, 12, 24 months	15 min
	Uptake	Participants	The *CollaboRATE* [22] is a 3-item scale that measures Shared-Decision Making from users’ perspective. Each of the three items is rated on a scale of 0 (“no effort was made”) to 9 (“every effort was made”). Range: 0–27 points.	Baseline, 12, 24 months	5 min
		Providers	The *Shared Decision Making Questionnaire – Physician Version (SDM-Q-Doc)* [23] will be employed to measure SDM at the provider level. This asks the clinician first to enter the health problem the consultation was about and which decision was made. The questionnaire continues with nine items about the steps in the SDM process, scoring at a six point scale that ranges from 0 (completely disagree) to 5 (completely agree). A total score can be calculated by summing the scores of all items. A high score indicates more SDM.	Baseline, 12, 24 months	10 min
		Providers and participants	The *Recovery Self-Assessment (RSA)* [24] provider and patient versions is a 32-item, self-administered rating scale that focuses on perceptions of recovery principles and overall quality of services. It captures both providers’ and patients’ perceptions that a specific recovery-oriented intervention, in this case OTCH, is agreeable, palatable or satisfactory. Each item is rated on a 5-point scale (1 = Strongly Disagree; 5 = Strongly agree). Higher scores indicating greater quality care. Range: 32–160 points.	Baseline, 12, 24 months	15 min
		Providers and partcipants	Ten ad-hoc questions regarding receipt of services that are central to OTCH including supported employment-education, family intervention/support, psychosocial interventions, and personal strenghts and resiliency training	Baseline, 12, 24 months	3 min
Service outcomes	Patient-centeredness	Participants	The *Youth Services Survey (YSS)* [25] is a scale that assesses perceptions about accessibility, quality, and impact of mental health service over a period of time. Only the first 15 items will be used in this study. Each item is rated on a 5-point scale from 1= “Strongly disagree” to 5 = “Strongly agree” (Range: 15–75 points).	Baseline, 12, 24 months	10 min
	Medication adherence	Participants	Measured by the *Brief Adherence Rating Scale (BARS)* [26] It consists of 4 items: 3 questions and an overall visual analog rating scale to assess the percentage of antipsychotic medication doses taken by the user in the past month (0–100%).	Baseline, 12, 24 months	5 min
	Retention	Participants	Time remaining in treatment will be estimated by counting the number of days between randomization to the time of the last mental health service received as defined by the RAISE-ETP report. The *Service Utilization and Resources Form for Schizophrenia (SURF)* [27] will be used to record users’ utilization of psychiatric and psychosocial rehabilitation services by conducting telephone contacts on a three-monthly basis. Range: from 0 to 365 days over a 12-month period; from 0 to 730 days over a 24-month period.	Every 3 months	15 min
Clinical outcomes	Psychotic symptoms	Participants	*Positive and Negative Syndrome Scale (PANSS)* [28] scale will be used to assess positive and negative symptoms (only the first 14 items). This scale includes seven rating points that represent increasing levels of psychopathology, from 1 (“absent”) to 7 (“extreme”). Range *7–*49 points.	Baseline, 12, 24 months	20 min
	Functioning	Participants	The *Social and Role Functioning in Psychosis and Schizophrenia* (SRFP) [29] scale asks for social, behavioral, and occupational difficulties associated with mental illness, including psychosis and schizophrenia. The scale rates functioning on a scale of 0 (“extreme role dysfunction”) to 10 (“superior social/interpersonal functioning”). Range: 7–70 points.	Baseline, 12, 24 months	20 min
	Recovery orientation	Participants	The *Questionnaire about the Process of Recovery (QPR)* [30] assesses users’ perceptions about recovery from psychosis. It has 15 items each scored on a 4-point scale ranging from 0 (“strongly disagree”) to 4 (“strongly agree”). Higher scores on the measure are indicative of recovery (Range: 0–60 points).	Baseline, 12, 24 months	15 min
Moderators	Poverty	Community-level	Administrative data from the *Chilean System of Social Protection* [31] will be utilized to estimate percentage of the population living below the national poverty lines (0–100%).	As available across study period	N/A
	Providers’ Attitudes to EBP	Providers	This will be measured by the *Evidence-Based Practice Attitude Scale* (EBPAS) [21] as described above under implementation outcomes.	Baseline	10 min
	Providers’ Recovery orientation	Providers	The *Recovery Self-Assessment (RSA)* [24] as described above under implementation outcomes	Baseline	15 min
	Symptoms	Participants	Measured by PANSS [28] as described above under clinical outcomes	Baseline	20 min
	DUP	Participants	The time between the onset of psychotic symptoms and initiation of treatment at a mental health clinic based on the FEP registry.	Baseline	NA
	Functioning	Participants	Measured by *SRFP* [29] as described above under clinical outcomes	Baseline	20 min
	Socio-demographics	Participants	Age (15–19, 20–24, 25–29, 30–34, 35–40 years), gender (male, female), ethnicity, education, employment, and marital status	Baseline	10 min

For estimating total health care costs, we will rely on both administrative data on expenditures for implementing and delivering OTCH, and interview data, collected every three months from participants on their use of services other than OTCH. Research assistants will document service use using the Service Use and Resource Form (Table 4) every three months, during the first year, to assure adequate recall [27, 32–39].

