**Methods:**

The Dynamic Adaptation Process will be used first to inform the adaptation and implementation of OTCH to the Chilean context. Then, a Hybrid Type 1 trial design will test its effectiveness and cost and evaluate its implementation using a cluster-randomized controlled trial (RCT) (*N* = 300 from 21 outpatient clinics). The OTCH program will be offered in half of these outpatient clinics to individuals ages 15-35. Usual care services will continue to be offered at the other clinics. Given the current COVID-19 pandemic, most research and intervention procedures will be conducted remotely. The study will engage participants over the course of 2 years, with assessments administered at enrollment, 12 months, and 24 months. Primary outcomes include implementation (fidelity, acceptability, and uptake) and service outcomes (person-centeredness, adherence, and retention). Secondary outcomes comprise participant-level outcomes such as symptoms, functioning, and recovery orientation. Over the course of the study, interviews and focus groups with stakeholders will be conducted to better understand the implementation of OTCH.

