**Trial status:**

The OTCH trial is currently recruiting participants. Recruitment started on March 1, 2021, and is expected to be completed by December 1, 2022. This is the first version of this protocol (5/12/2021).

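### Retention, a primary outcome, is counted from randomization, but only clinics are randomized and participants enrol later; the start point and the service-use schedule behind it need correcting

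*Protocol article*

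**What the plan says.** The Abstract lists retention among the primary outcomes: "Primary outcomes include implementation (fidelity, acceptability, and uptake) and service outcomes (person-centeredness, adherence, and retention". The retention row of Table 4 measures it by "counting the number of days between randomization to the time of the last mental health service received", with a range of 0 to 365 days at 12 months and "from 0 to 730 days over a 24-month period". The row refers to an outside report for its definition and takes its data from the service-use form (SURF), completed by telephone every three months.

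The Randomization section allocates clinics, not people: "The 21 participating clinics will first be divided into two groups based on the poverty level of the catchment area". They are then matched and allocated within blocks. On timing it says that "the randomization (and notification) will be done at the start of the project". One clinic from each arm then enters per month.

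Under Recruitment, a clinic refers participants only after it has entered the study. Trial status gives the window: "Recruitment started on March 1, 2021, and is expected to be completed by December 1, 2022". The Abstract starts the assessment clock at enrolment, with visits at 12 and 24 months.

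On the service-use form, the cost paragraph under Data collection says: "Research assistants will document service use using the Service Use and Resource Form (Table 4) every three months, during the first year". The opening of the same section says that every instrument is given at baseline, 12 and 24 months. Aim 3 costs care over 24 months.

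**The concern.** A count of days needs a start date that exists for each person and means the same for everyone. Here the named start is an event of the clinic, and it comes before the person's enrolment by a gap that depends on when they were recruited. An analyst who follows the definition literally would compute a different variable from one who follows the range printed beside it.

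Retention is tested as a primary outcome under Aim 1. Its 12-month value is also one of the service outcomes tested as mediators under Aim 2b, so an error in the start point would reach both analyses.

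The second problem is the data source. A range to 730 days and a 24-month cost horizon both need service-use data in year two, yet one paragraph confines the three-monthly form to year one.

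**Working it through.** **Inputs**
- Start of count: randomization (Table 4, retention row).
- Unit and time of randomization: clinics, at the start of the project (Randomization). No calendar date is given.
- Recruitment: 1 March 2021 to 1 December 2022 (Trial status).
- Stated maxima: 365 days at 12 months and 730 at 24 months (Table 4).

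**Length of the window.** 1 March 2021 to 1 March 2022 is 365 days; 1 March to 1 December 2022 is 275 days. 365 + 275 = 640 days, about 21 months.

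**Can the stated ranges be reproduced?** Let L be the days from clinic randomization to the participant's enrolment. For someone still in care at the visit:
- counting from enrolment, the maximum is 365 or 730 for everyone, as stated;
- counting from randomization without a cut, the maximum is L + 365 or L + 730;
- stopping at 365 or 730 days from randomization, the observable days in care are max(0, 365 − L) or max(0, 730 − L).

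The table places randomization on the first recruitment day. This is an assumption, and it keeps L small because the Randomization section puts allocation before the preparatory-phase data collection.

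| Enrolment | L | Uncut maximum, 12 / 24 months | Observable days if cut, 12 / 24 months |
|---|---|---|---|
| First day | 0 | 365 / 730 | 365 / 730 |
| Mid-window | 320 | 685 / 1050 | 45 / 410 |
| Last day | 640 | 1005 / 1370 | 0 / 90 |

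If randomization came 3, 6 or 12 months before first recruitment (assumed; 30.4375 days per month), the last enrolee's uncut 24-month maximum would be 1461, 1553 or 1735 days. Only the enrolment origin reproduces 365 and 730 for every participant.

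**Effect on the comparison.** On the uncut reading, score = L + days in care. The difference between arms in mean score is therefore the difference in mean L plus the difference in mean days in care, and any imbalance in L passes through one for one. The document gives no figure for that imbalance.

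**Service-use schedule, side by side**
- Table 4, retention row: every three months, range to 730 days, no year-one limit.
- Cost paragraph: the same form, with a reference to Table 4, every three months in the first year.
- Opening of Data collection: all instruments at baseline, 12 and 24 months.
- Aim 3: costs over 24 months.

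Three-monthly contacts in year two fall at months 15, 18, 21 and 24. Month 24 is kept by the general statement, so at most three (15, 18 and 21) are in doubt.

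**The case against.** The strongest reply is that the same table row resolves the wording. Its ranges fit only a count from the participant's own entry, the assessment clock starts at enrolment, and the section on qualitative assessments also dates its 6- and 18-month interviews from randomization in a loose way. Enrolment was very probably meant. That stands, and it makes the correction small. It does not remove the need for it, because the operational rule for a primary outcome names a different date.

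A second reply is that clinics enter in pairs, one per arm each month, so entry is balanced over calendar time. This also stands, as a limit on bias. It balances clinic entry but does not fix how fast each clinic then enrols.

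A third is that the year-one limit sits in a paragraph about costs, while retention has its own row. That is a fair reading, but the limit then conflicts with the 24-month cost aim, so the passages need reconciling either way.

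A reader might go further in three ways that the document does not support:
- That late enrolees will look well retained, or that the intervention arm gains a false benefit. Uncut, a long wait inflates the score; cut at 365 and 730 days, it shortens the time in which care can be observed. No lag between arms is reported, and any loss of standardized effect would need an assumed spread of retention and an assumed enrolment pattern.
- That half of the eight quarterly contacts are lost. The month-24 contact remains.
- That the hierarchical linear model must be replaced by a survival or restricted-mean analysis. Mean days in care to a fixed horizon is a legitimate target, the plan provides for checking distributions, and the choice is open to debate.

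**Conclusion.** The point holds for the start of the count and for the data schedule. The stated rule and the stated ranges for retention cannot both be right when clinics are randomized at project start and participants enrol over the next 640 days or more. Taken literally, the variable exceeds its own maximum by up to 640 days if randomization fell on the first recruitment day, and by more if it fell earlier. This rests only on the document's dates and that one placement.

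The size and direction of any effect on the treatment contrast cannot be fixed from the document. The service-use conflict is real but narrower: it concerns months 15, 18 and 21, and it may be confined to the cost data.

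**What to change.** 1. In Table 4, define retention as days from the participant's own enrolment (baseline) date to the last service, capped at 365 and 730 days from that date. This matches the printed ranges and the assessment clock.
2. State once that the service-use form is collected every three months through month 24, as Table 4 and the 24-month cost aim require. Bring the cost paragraph and the opening of Data collection into line with it.

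The first change is wording only, since visits are already timed from enrolment. The second adds nothing if Table 4 is being followed. If practice has followed the year-one limit, the extra work is at most 3 contacts × 300 participants × 15 minutes (the time in Table 4) = 13,500 minutes, or 225 hours. Both should be settled before retention is analysed.
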